**Design:**

The AFFELECT trial (NCT04267159) is an investigator-initiated, prospective, unblinded randomized controlled non-inferiority trial comparing experimental delayed rhythm control (elective CV performed within 5–9 days after the index visit) to standard acute rhythm control (CV performed in ED) in patients with recent-onset (duration <48 h) symptomatic AF/AFL suitable for rhythm control. A total of 500 patients are randomized in a 2:3 ratio to the acute and delayed groups, respectively, accounting for a possible one-third unplanned early CV rate in the delayed group due to higher symptom burden. Unplanned early CV means that patients with unbearable symptoms are offered the option for an earlier CV (before the 5–9 days target timeline) if needed. Patients randomized to delayed group are discharged immediately after adequate heart rate control (heart rate <110 bpm) and anticoagulation and are scheduled an appointment for delayed CV at a cardiology outpatient clinic (in transoesophageal echocardiography guidance if required). Patients randomized to acute CV undergo cardioversion in the ED within 48 h of arrhythmia onset and are assigned to a cardiologic outpatient clinic visit also within 5–9 days. The primary end-point is the presence of sinus rhythm on electrocardiogram at 4 weeks after the outpatient clinic visit.

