### Patient eligibility

Patients with recent-onset AF/AFL (<48 h) who are suitable for acute rhythm control by CV as first-line treatment are screened for eligibility of participating in the study. These include both patients arriving to the ED directly and by referral. Patients considered for the study must be suitable for both acute and delayed rhythm control. The inclusion and exclusion criteria are described in *Table 1*. Possible high heart rate (>110 bpm) is acutely controlled before the final eligibility assessment, primarily using betablockers (usually bisoprolol), in accordance with guidelines established by the European Society of Cardiology (ESC)^9^ and American College of Cardiology/American Heart Association.^19^

**Table 1 oeag060-T1:** Inclusion and exclusion criteria

Inclusion criteria	Exclusion criteria
Age 18 years or older	Cardioversion not possible within 48 h if randomized to acute cardioversion
Recent-onset AF or AFL (<48 h)	Haemodynamically unstable: mean arterial pressure <60 mmHg
Planned acute rhythm control (acute CV) for the arrhythmia^a^ Heart rate ≤110 beats/min at rest either w/o medication after adequate rate control therapy	Cardioversion needed for some other somatic cause (for example poor clinical condition due to some other somatic cause requiring immediate restoration of sinus rhythm)^a^ Major co-existing illness predisposing to AF/AFL, including decompensated heart failure, ongoing myocardial infarction or hospitalization due to heart failure within 1 month of the ED visit, or severe valvular heart disease requiring urgent treatment.
	Anticoagulation not possible or safe due to poor co-operation or for clinical condition (for example chronic alcoholism, severe liver dysfunction, or history of severe spontaneous bleeding or bleeding under anticoagulation).
	Mitral stenosis or mechanical heart valve (any position)
	Need for prolonged hospitalization (over 24 h) due to any cause.
	Exceptionally high risk of thromboembolism (e.g. history of thromboembolism regardless of anticoagulation)
	Transoesophageal echocardiogram is contraindicated
	Participation unsuitable due to any somatic or psychiatric condition^a^
	Unable or unwilling to provide written informed consent

AF, atrial fibrillation; AFL, atrial flutter; ED, emergency department.

^a^At the discretion of the attending physician.

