### Rhythm control and anticoagulation strategy in the delayed rhythm control group

Patients randomized to delayed rhythm control are discharged immediately after their anticoagulation status has been secured and adequate rate control (heart rate <110 bpm) is ensured. The effectiveness of pre-existing anticoagulation therapy is verified (adherence to the use of direct oral anticoagulants [DOACs] or by verifying INR values for warfarin users) and patients with no prior anticoagulation are initiated on a DOAC regardless of the CHA_2_DS_2_-VASc score. However, if a patient experiences spontaneous return to SR before discharge and has very low thromboembolic risk (CHA2DS2-VASc = 0), no anticoagulation is initiated. Before discharge from the ED, or at latest the following working day, patients are scheduled for an appointment at a cardiologic outpatient clinic within 5–9 days, which includes the delayed (elective) CV. If the patient feels that the rhythm has spontaneously restored to SR before the planned CV, an ECG is taken to confirm this event on the next working day, at the latest.

The patient is referred to acute CV in the ED as soon as possible (with a transoesophageal echocardiography [TEE] guided CV for patients without previous anticoagulation therapy for at least 3 weeks, which has been shown to be safe^21,22^) if the patient randomized to delayed rhythm strategy feels that a more expedient CV is called for due to unbearable symptoms. All patients without previous anticoagulation for at least 3 weeks are advised of this option before consenting to the trial, including the possibility of TEE-guided CV. Patients also have the option to consult research personnel during office hours or go to the ED if the symptoms are unbearable during night-time or during weekend.

Patients are advised to seek acute medical care directly if they suspect that AF or AFL has recurred, or if they otherwise require urgent evaluation and/or care, regardless of whether study personnel have been contacted. This recommendation applies from discharge from the ED up until the first-month ECG control. If arrhythmia symptoms persist for a few hours and AF or AFL is recorded, the patient is referred to ED for implementation of acute rhythm control. If rate control is selected as the preferred strategy by the treating cardiologist at any point in the study, the ECG is, nevertheless, recorded at the earliest possible opportunity.

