### Primary and secondary end-points

The primary end-point in this study is the presence of sinus rhythm verified by ECG on a predefined date 4 weeks after the visit to the outpatient clinic. The primary analysis will follow the intention-to-treat principle, comparing randomized groups irrespective of spontaneous conversion or expedited CV in the delayed group. A per-protocol analysis will be conducted as a sensitivity analysis in accordance with recommendations for non-inferiority trials.^25^ Early unplanned CV (0–4 days after ED visit) due to unbearable symptoms in the delayed rhythm control strategy is considered a prespecified intercurrent event and leads to exclusion from the per-protocol analysis. This exclusion is performed to study the non-inferiority of successfully delaying the CV by at least 5 days from presentation to ED. Patients with missing end-point data are excluded from the analyses, and the number of patients with missing data is reported. Secondary end-points include the overall recurrence of AF or AFL, the number of required CVs and duration of ED stay, the need to use antiarrhythmic drugs within the first month, unplanned CV rate within the first week due to unbearable symptoms (elective approach), cardiovascular events—including events monitored for safety, and quality of life. The details of the end-points are listed in *Table 2*.

**Table 2 oeag060-T2:** End-points of the randomized controlled AFFELECT trial

Outcome measure	
PRIMARY OUTCOME	
Sinus rhythm	Prevalence of sinus rhythm in the treatment arms measured by electrocardiography at 1 month. The ECG is taken on a prespecified day aiming for the closest working day 4 weeks after the outpatient clinic visit (4–5 weeks after original ED visit).
SECONDARY OUTCOMES	
Number of cardioversions	First week after randomization (before preplanned outpatient clinic visit) One month after out-patient clinic (before control ECG) Overall (from randomization to 1 month control ECG)
Unplanned CVs in delayed cardioversion group	The number of subjects needing unplanned cardioversion before preplanned outpatient clinic visit (within four days after randomization) due to medical reasons or due to subjectively perceived unbearable symptoms (EHRA III or IV).

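### The per-protocol exclusion in the delayed arm depends on the reason for early cardioversion, although its stated purpose is timing and Table 2 also foresees early cardioversion for medical reasons

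*Protocol article*

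**What the plan says.** Under Primary and secondary end-points, the article makes intention-to-treat the primary analysis and per-protocol a sensitivity analysis. It then states the exclusion rule for the delayed arm: "Early unplanned CV (0–4 days after ED visit) due to unbearable symptoms in the delayed rhythm control strategy is considered a prespecified intercurrent event", with removal from the per-protocol analysis as the consequence. The next sentence gives the purpose: "This exclusion is performed to study the non-inferiority of successfully delaying the CV by at least 5 days from presentation to ED".

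Table 2, in the same section, defines the secondary outcome of unplanned CV in the delayed arm. It counts patients who need CV within four days of randomization "due to medical reasons or due to subjectively perceived unbearable symptoms (EHRA III or IV". The running text of that section describes the secondary end-point more briefly, as "unplanned CV rate within the first week due to unbearable symptoms (elective approach".

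Two other places bear on the meaning. The Abstract (Design) explains the term: "Unplanned early CV means that patients with unbearable symptoms are offered the option for an earlier CV". Sample size calculations and considerations says that unplanned early CV in the delayed arm leads to per-protocol exclusion and attaches no reason in that sentence. It then justifies the assumed one-third by symptom severity.

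**The concern.** The rule and its purpose select different patients. The purpose depends on when the CV took place. The rule depends on when and why. Table 2 shows that the authors expect a second kind of reason, so the gap is not an empty category. The eligibility criteria in Table 1 reduce it at entry but cannot prevent medical events after discharge.

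Two things are at stake. First, the per-protocol analysis is the named sensitivity analysis for the non-inferiority claim, and the 2:3 allocation was chosen because of this exclusion. Read literally, the analysis does not quite answer the question it is said to answer. Second, allocation is unblinded, and under the literal rule membership of the per-protocol set turns on the reason recorded for each early CV. The EHRA III–IV anchor in Table 2 limits that judgement only in part, because the same line describes the symptoms as subjectively perceived.

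**Working it through.** **Step 1: the texts side by side.**
- Rule (Primary and secondary end-points): days 0–4, unbearable symptoms, delayed arm.
- Purpose (next sentence): CV delayed by at least 5 days; no reason mentioned.
- Table 2: within four days; medical reasons or unbearable symptoms.
- Sample size section: unplanned early CV; no reason in the sentence on exclusion.
- Abstract: unplanned early CV explained through unbearable symptoms.

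Take a delayed-arm patient cardioverted on day 2 for a medical reason. The literal rule keeps this patient. The purpose would exclude the patient, and so would the sample size sentence if taken alone. Table 2 counts the patient as an unplanned early CV. No sentence says which applies to the per-protocol set.

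**Step 2: reproduce the plan's figures.** Inputs from the sample size section: 90% sinus rhythm (taken as equal in both arms), margin 10 points, one-sided alpha 0.025, power 90%.
- n per arm = 2 × 0.90 × 0.10 × (1.960 + 1.282)² / 0.10² = 189.1, rounded up to 190, so 380 in total. This matches.
- 190 × 3/2 = 285; 285 × 2/3 = 190; 190 + 285 = 475; 475 + 25 = 500. These match too. None of these figures is in dispute.

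**Step 3: room to the margin.** With 190 acute patients, SE = sqrt(0.09/190 + 0.09/n), where n is the delayed per-protocol number. The half-width is 1.96 × SE, and the room is 10 minus the half-width.
- n = 190: SE 3.078 points, half-width 6.03, room 3.97.
- n = 285: SE 2.810 points, half-width 5.51, room 4.49.

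**Step 4: effect of keeping such patients.** The document gives no rate. Assume k = 2 to 10 patients among n, whose sinus rhythm prevalence differs by d = 10 to 30 points from the rest. Shift = k × d / n.
- n = 190: 2 × 10/190 = 0.11; 10 × 30/190 = 1.58 points.
- n = 285: 2 × 10/285 = 0.07; 10 × 30/285 = 1.05 points.

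A wider assumption starts from 500 patients split 200 to 300, with one-third of the delayed arm (100) cardioverted early. If 5 to 30 of these 100 were for medical reasons and stayed in, and their prevalence were 70% to 100% against 90%:
- 5 kept: 5 × (−20)/205 = −0.5 to 5 × 10/205 = +0.2 points.
- 30 kept: 30 × (−20)/230 = −2.6 to 30 × 10/230 = +1.3 points.

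The direction is unknown. No shift here reaches the 4.0 points of Step 3.

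**Step 5: power cost of excluding them.** Power = Φ(10/SE − 1.96), with 190 acute patients.
- Delayed 190: 90.1%; 188: 90.0%; 180: 89.3%; 170: 88.4%.
- Delayed 285: 94.5%; 275: 94.2%.

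**The case against.** The strongest reply is that the section explains itself. The purpose sentence stands next to the rule and tells the reader how to apply it: a patient cardioverted on day 2 was not delayed by 5 days, whatever the reason. The mention of unbearable symptoms also looks like shorthand, since the running text uses the same phrase for the secondary end-point that Table 2 widens to medical reasons. The Abstract describes an option offered to patients and does not speak of the per-protocol set. Finally, the rule is not said to be exhaustive, and a fuller definition may stand in a document not shown.

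Much of this stands. A wider intent is plausible, and the effect is small. But the article itself fixes the event, window, reason, consequence and purpose, so the objection is to a stated rule that misses its purpose, not to detail left for later. The sample size section drops the reason in one sentence and then returns to symptom-driven requests, and the Abstract points to the narrow meaning. Two statisticians could build different per-protocol sets from this text.

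A reader might go further and infer that the plan definitely keeps patients with medical-reason CV. The documents do not support that; they leave it open. Nor is early CV for a recurrence an error in the plan, because the section on the delayed arm directs it: "If arrhythmia symptoms persist for a few hours and AF or AFL is recorded, the patient is referred to ED".

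**Conclusion.** The point holds as a minor one. The exclusion is worded by reason, its purpose is timing, and Table 2 names a reason that the wording leaves out. Only the per-protocol sensitivity analysis is affected.

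A reader might infer that the non-inferiority conclusion or the sample size is at risk. Neither follows. The primary analysis compares the randomized groups regardless of expedited CV, and the total of 500 does not depend on this wording. The number of patients is probably small, because Table 1 already excludes haemodynamically unstable patients and those with "Cardioversion needed for some other somatic cause". On the assumed 2 to 10 patients differing by 10 to 30 points, the shift is 0.1 to 1.6 points; on the wider assumption it is −2.6 to +1.3 points. Neither alone uses up the roughly 4 points of room, given 90% sinus rhythm in both arms. These counts and differences are assumptions, since the documents give none.

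**What to change.** Define the per-protocol intercurrent event as any unplanned CV on days 0–4 in the delayed arm, whatever the reason. Use the same wording in the end-point section, Table 2 and the sample size section. Recruitment is reported as ongoing, so this can be settled before the analysis.

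The change costs one definition and a slightly smaller per-protocol set: power falls from about 90.1% to 89.3% if 10 of 190 are dropped. The exclusion still applies to one arm only, as it does now.

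The wider rule also removes patients who returned to sinus rhythm, relapsed and were cardioverted by day 4 as the protocol directs. Optionally, report a further sensitivity result that keeps patients whose early CV followed an ECG-documented return to sinus rhythm. Its limit should be stated. The protocol plans the ECG ("an ECG is taken to confirm this event on the next working day, at the latest") only when the patient feels that the rhythm has converted. Unnoticed conversions will have no such ECG, and a relapse before the next working day can be missed.

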### Data collection and follow-up

Each patient completes a form requesting full disclosure of medical status and history in the ED, and this information is verified using electronic health records and written medical records which cover all prior specialized healthcare visits and the patients’ current medications. Furthermore, ED data on patient status (including haemodynamic parameters and laboratory values), received medical treatments and additional diagnostics are also collected.

After the outpatient clinic visit, a standard 12-lead ECG is recorded for all patients after 4 weeks (closest working day) from cardiology outpatient clinic visit. The date for this ECG is predefined so that the rhythm status is measured as it is at that date. In addition, patients are asked to fill in a symptom severity questionnaire also disclosing possible shorter arrhythmia episodes (not captured by ECG recordings) occurring during this time. A standard 12-lead ECG is also repeatedly recorded 3 months after the outpatient clinic.

All patient health records, and the Finnish Care Register for Healthcare are reviewed 1 and 3 months after the outpatient visit, as well as at 1 and 5 years after enrollment. Data on especially subsequent visits to ED due to AF/AFL and all other visits to specialized healthcare including major adverse cardiac and cerebrovascular events are recorded.

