### Sample size calculations and considerations

The power calculation indicated that 500 randomized patients are required to ensure 90% power (one-sided alpha level of 0.025) to reliably demonstrate non-inferiority, should the elective treatment prove inferior with respect to the primary end-point. The experimental treatment (elective approach) will be considered inferior if the lower bound of the 95% confidence interval for the difference in sinus rhythm prevalence (elective minus acute) falls below −10%. The calculation is based on the assumption that the prevalence of sinus rhythm in the control population is 90%. A 10% margin in sinus rhythm prevalence between the treatment groups is deemed clinically acceptable, as the prevalence of sinus rhythm can fluctuate daily among patients, and a variation of less than 10% is unlikely to affect the long-term prognosis of the participants. If patients were randomized into two equal groups, the total sample size would be 380 patients. However, a 2:3 randomization ratio was chosen to conservatively account for the anticipated occurrence of unplanned early CV in the delayed strategy group, which would lead to exclusion from the per-protocol population, as patients were informed about this possibility prior to randomization. For every patient randomized to the acute CV treatment group (at least 190 patients), three patients will be randomized to the elective CV treatment group (at least 285 patients). This randomization ratio accounts for the possibility that up to one-third of patients may request more urgent CV after randomization (with no unplanned CVs for unbearable symptoms the minimum number of patients would be thus 190 + 190 patients). This assumption was based on previous findings from the FinFib study, which indicated that up to one-third of patients undergoing emergency CV experience symptoms severe enough to interfere with daily life (EHRA Class III–IV)^6,20^ and therefore they might need an earlier CV. Considering the potential loss of patients to follow-up, the study aims to recruit approximately 5% (25) more participants than the minimum required by the power calculations (475 patients), resulting in a total of 500 patients.

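### The primary analysis is labelled intention-to-treat but drops every patient without an end-point ECG, including any who die; unequal loss between arms would then bias towards non-inferiority

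*Protocol article*

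**What the plan says.** In the protocol article, section Primary and secondary end-points, the end-point is "presence of sinus rhythm verified by ECG on a predefined date 4 weeks after the visit to the outpatient clinic". On the analysis set the same section states: "The primary analysis will follow the intention-to-treat principle, comparing randomized groups irrespective of spontaneous conversion or expedited CV in the delayed group". A little further on it states: "Patients with missing end-point data are excluded from the analyses, and the number of patients with missing data is reported". The exclusion refers to the analyses in the plural, so it covers the per-protocol comparison too: "A per-protocol analysis will be conducted as a sensitivity analysis in accordance with recommendations for non-inferiority trials".

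The section Sample size calculations and considerations expects about 5% loss (25 of 500) and deals with it by recruiting more patients. On the margin it says: "A 10% margin in sinus rhythm prevalence between the treatment groups is deemed clinically acceptable". Non-inferiority fails if the lower 95% bound for delayed minus acute is below −10 percentage points.

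**The concern.** Dropping randomized patients because their outcome is missing gives a complete-case analysis. The label and the rule therefore do not match, and the rule is stated outright in the article.

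A patient who dies before the ECG date cannot have the ECG. Under the rule that patient leaves both numerator and denominator, so a death in either arm never counts against the arm.

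Loss could differ between arms here. Allocation is open. The ECG date is counted from the clinic visit, and in the delayed arm that visit is also where the planned cardioversion takes place. A delayed-arm patient who does not attend may miss both. The direction is not certain, since a non-attender may have converted spontaneously. If missing delayed patients are more numerous, or do worse, than missing acute patients, the observed difference moves towards non-inferiority. The trial's single confirmatory claim is what is at stake.

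**Working it through.** **Inputs from the article.** 500 patients randomized 2:3, so 200 acute and 300 delayed; control rate 90%; margin 10 points; one-sided alpha 0.025; power 90%; expected loss 25 patients. **Assumed, because the article does not give them:** how the missing patients split between arms, and their rhythm.

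**Step 1: the plan's own figure.** With equal true rates of 90%, n per arm = (1.960 + 1.282)² × 2 × 0.9 × 0.1 / 0.10² = 189.1, so 190 per arm and 380 in total. Allowing for one-third early cardioversion, 190 / (2/3) = 285, and 190 + 285 = 475. Allowing for 5% loss, 475 / 0.95 = 500. The sample size reproduces. Complete-case power at 190 and 285 is Φ(0.10/0.0281 − 1.96) = 94.5%, so the issue is bias and not lost power.

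**Step 2: effect on the confidence bound.** Assume 5% missing in each arm (10 acute, 15 delayed) and 90% observed in both: 171/190 and 256.5/285. Lower bound = d − 1.96 × √(p_A(1−p_A)/n_A + p_D(1−p_D)/n_D).

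| Handling of the 25 missing patients | Acute | Delayed | Difference (points) | Lower bound |
|---|---|---|---|---|
| Excluded (the stated rule) | 171/190 = 90.0% | 256.5/285 = 90.0% | 0 | −5.5% |
| Failure in both arms | 171/200 = 85.5% | 256.5/300 = 85.5% | 0 | −6.3% |
| Acute 90%, delayed 50% in sinus rhythm | 180/200 = 90.0% | 264/300 = 88.0% | −2.0 | −7.6% |
| Worst case: all acute in sinus rhythm, no delayed | 181/200 = 90.5% | 256.5/300 = 85.5% | −5.0 | −10.7% |

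Only the last row crosses −10%. If two of the 15 missing delayed patients are in sinus rhythm and all missing acute patients are too, the bound is −9.97%. With 10% missing per arm and the 90%/50% pattern, it is (243 + 15)/300 = 86.0% against 90.0%, lower bound −9.7%.

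**Step 3: effect on the error rate at the margin.** Take true rates of 90% (180/200) and 80% (240/300). Remove the missing patients, then compute P(declare non-inferior) = Φ((d + 0.10)/SE − 1.96).

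- Missing unrelated to rhythm within arm: d = −10.0 points, error 2.5%. No bias.
- 5 acute and 20 delayed missing, half in each arm not in sinus rhythm: (180 − 2.5)/195 = 91.0% and (240 − 10)/280 = 82.1%. d = −8.9 points, SE 0.0307, error 5.5%.
- The same 5/20 split, all missing not in sinus rhythm: 180/195 = 92.3% and 240/280 = 85.7%. d = −6.6 points, error 22.5%.
- 10 and 15 missing (5% each), 10% of the acute and 50% of the delayed missing not in sinus rhythm: d = −8.4 points, error 7.2%.
- 10 and 15 missing, all not in sinus rhythm in both arms: 180/190 = 94.7% and 240/285 = 84.2%. d = −10.5 points, error 1.6%. Slightly conservative.

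The bias towards non-inferiority therefore needs loss that differs between arms in amount or in outcome.

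**The case against.** The strongest reply is that the planned loss is small and only an extreme pattern overturns a clear result. That stands: from 90% against 90%, at most one of 15 missing delayed patients could be in sinus rhythm for the bound to pass −10%, and then only if all the missing acute patients are. Nor do the documents show that loss will differ between arms; the uneven splits above are assumptions.

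Three stronger readings are tempting, and the article does not support them.

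- A reader might infer that any stroke or hospitalization removes the patient. The rule removes only patients whose end-point is missing. A 12-lead ECG can still be recorded after such events, and they are also collected separately as safety outcomes. Death is the one event that necessarily removes the ECG.
- A reader might count the lack of a stated missing-data sensitivity analysis as a fault. The article is condensed and the analysis plan is not shown, so such an analysis may exist there. The criticism is of the rule that the article does state.
- A reader might assume that data already held can replace the missing ECG. The article says "All patient health records, and the Finnish Care Register for Healthcare are reviewed 1 and 3 months after the outpatient visit", but describes that review as collecting visits and events, not rhythm on the target date. Interim ECGs are taken on clinical indication and may over-represent arrhythmia. These sources can inform imputation only.

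The remedy below is also one defensible package among several.

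**Conclusion.** The point holds in this limited form. The stated rule makes the primary analysis complete-case, which the intention-to-treat label does not describe, and it discards deaths before the ECG. Whether this biases the result depends on loss that cannot be known in advance. With similar loss in both arms the effect is nil or slightly conservative; with more loss, or worse rhythm among the lost, in the delayed arm it favours non-inferiority. Under the assumed patterns at the planned 25 missing patients, the lower bound falls by about 1 to 2 points in moderate cases (−5.5% to −6.3% or −7.6%) and by about 5 points in the worst case. False non-inferiority at the margin ranges from 1.6% to 22.5%, with 5.5% for the 5/20 split in which half of the missing are failures. It would be wrong to conclude that the rule must favour non-inferiority, or that ordinary 5% loss would overturn a clear result. This should be fixed, but it does not invalidate the design.

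**What to change.** Replace the exclusion rule, so that the primary analysis includes all randomized patients:

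- Count death before the ECG as not in sinus rhythm.
- Multiply impute other missing ECGs within arm from site, baseline factors, rhythm at the clinic visit and the 3-month ECG. Use clinically indicated ECGs only as auxiliary information.
- Add a tipping-point analysis that reports how low sinus rhythm among missing delayed patients must be, for given rates among missing acute patients, before the lower bound passes −10%.
- Keep the complete-case result as a sensitivity analysis, and report missing numbers and reasons by arm.

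Counting every missing ECG as failure would be simpler but is not neutral: with 90% observed in each arm and 5% missing per arm, power falls from 94.5% to Φ(0.10/0.0321 − 1.96) = 87.5%.

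The cost is a change of wording, a little programming and possibly a slightly wider interval. No new data are needed. The article describes recruitment as ongoing, so the rule can still be changed, and dated, before the final analysis.
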